### HeartLink Practice Recruitment

*HeartLink* is set in the ACT, Australia, and is a pilot intervention in six general practices, which have been selected to broadly represent of the socioeconomic and demographic population in the region.

The practices that are recruited will be required to meet a number of inclusion criteria, including: (1) agreement that the patient has no additional payment to make from participation in the first recall visit and the 12 month follow-up visit, (2) agreement to have at least one practice nurse on staff to support the intervention, and (3) have the PEN Computer Systems Pty (Sydney, Australia) Clinical Audit Tool software.

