### HeartLink Intervention Description

#### Enhanced Usual Care in General Practice for Patients at High Risk of Cardiovascular Disease

The aims of the *HeartLink* pilot are to work with general practices to enhance care in relation to identification, recall, assessment, and management of patients at high risk of CVD. The intervention follows the evidence-based “5A’s” approach, with key steps integrated across the pilot design [26]. Upon recruitment, support will be provided to all of the participating general practices to audit their patient data, establish or improve data quality processes, and, where required, encourage processes to improve the levels of preventative activities such as measurement and recording of patient blood pressure. These actions are expected to maximize the patient numbers for recruitment, and will support the broader aims of the pilot to improve systems for the prevention and management of CVD in the pilot practices.

The PEN Computer Systems Pty Clinical Audit Tool CVD risk report will be used for the population of each practice, except those not attending the practice for more than two years, as it is likely that they are no longer patients of the practice or do not have a regular general practitioner (GP) at the practice. The patients identified as having a risk score of >15% on their most recently recorded clinical information will be sent a letter asking them to visit for a “heart and stroke” check [4]. The patients whose most recent cholesterol measures are greater than six months old will be sent a pathology request form along with their recall letter to encourage them to update their lipid levels before they attend their recall visit.

When patients arrive for their recall visit, they will have their CVAR recalculated by the practice nurse before a consultation with their GP.

As part of the recall visit to the general practice at baseline and 12 months, the CVD risk factor information required to calculate the absolute risk will be collected. The practice nurse in the clinical environment will measure the blood pressure, and the cholesterol level measurement (total and high-density lipoprotein cholesterol) will have been undertaken by a commercial pathology service provider upon referral from the GP prior to the visit. The smoking status, defined as smoker or nonsmoker (self-reported), will be recorded.

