### Data Analysis

#### Quantitative Data Analysis

Changes in the CVAR will be reported at the total practice population level, but also analyzed by each practice. The primary analysis will be done on an Intention to Treat basis. The CVAR was chosen as the primary health outcome, as it represents an all around measure of the *HeartLink* intervention’s ability to meet its objectives.

An analysis of the quantitative data collected from the clinical data and the participant survey will be undertaken. Univariate comparisons between the pre and post intervention groups will be conducted using a chi-square test for equal proportion (or Fisher’s exact tests where numbers are small), and reported as numbers and percentages. Continuous normally distributed variables will be compared using student’s *t* tests and reported as means (95% confidence interval). Nonnormally distributed data will be compared using Wilcoxon signed rank tests.

The *HeartLink* pilot data will be used to estimate population proportions (and confidence intervals) for those at high risk of CVD in the ACT. This data will also generate planning information for a future larger study. The intercluster correlation coefficient, effect size, and standard deviation will be examined to help determine sample size calculations, cluster size, and number of clusters.

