### Limitations of the Study Protocol

There are a number of limitations of this study. Case study approaches have often been criticized for their lack of generalizability, and their lack of rigor. To address this, a sound research design has been developed that follows a logical process [22]. The multiple sources of data and the addition of the preexperimental component should add rigor by allowing the cross-validation of the interpretation of the study findings.

The *HeartLink* intervention itself has limitations that include the small scale of the intervention, “opt in” in the sample of practices, and the intervention occurring in one relatively small city of approximately 340,000 people. Given its pragmatic design, the study has limitations in standardizing some aspects of the intervention protocols and data collection, within busy general practices with a varied workforce and a wide range of skill sets. That acknowledged, the MoFoP study and the *HeartLink* intervention are designed to inform a larger cluster randomized controlled trial to evaluate the effectiveness of using a larger number of control and intervention practices, and to better understand the effectiveness and generalizability across the primary health care sector as a whole.

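### The planned confidence intervals for proportions at high cardiovascular risk in the ACT have no sampling basis: the data come from six selected, volunteer practices and describe only their recent attenders

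*Protocol article*

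**What the plan says.** Under Quantitative Data Analysis, the protocol article states that HeartLink "pilot data will be used to estimate population proportions (and confidence intervals) for those at high risk of CVD in the ACT". The sentence has no qualification, and the article defines neither numerator nor denominator. It gives no method for the interval. The intercluster correlation is to be examined, but only to plan a later trial.

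The data source is described elsewhere in the article:

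- **HeartLink Practice Recruitment.** HeartLink "is a pilot intervention in six general practices, which have been selected to broadly represent of the socioeconomic and demographic population in the region". Practices must also accept a no-extra-payment condition for two visits, agree to have a practice nurse, and "have the PEN Computer Systems Pty (Sydney, Australia) Clinical Audit Tool software".
- **Enhanced Usual Care in General Practice.** The audit-tool risk report covers each practice's population "except those not attending the practice for more than two years". It scores patients on their most recent recorded data. Practices are also helped to audit and improve that recording.
- **HeartLink Participant Eligibility and Recruitment.** Enrolled patients must have CVAR >15% and no established CVD, diabetes or previous cardiovascular event.
- **Limitations of the Study Protocol.** The authors list the small scale, the voluntary entry of practices, and "the intervention occurring in one relatively small city of approximately 340,000 people".

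**The concern.** A confidence interval for a territory-wide proportion expresses sampling error around a population value. That needs either a known chance of selection for practices and patients or a stated model that stands in for it. The article offers neither. It names the whole ACT as the target, yet its own limitations section concedes that the practices volunteered.

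If the sentence is followed as written, the result will be read as an ACT figure with known precision. In fact it would describe people who attended one of six practices in the past two years and whose risk factors happened to be recorded. The same paragraph says that the data will generate planning information for a larger study. An ACT proportion with an unsupported interval could therefore mislead recruitment planning as well as policy readers.

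**Working it through.** **Figure in the plan.** The only sample size stated is 30 patients in each of six practices: 6 x 30 = 180. It reproduces, but it rests on resources and practice burden, with no precision target for any proportion.

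**Which data could give the proportion?** The sentence can be read in two ways.

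1. *Prevalence of high risk.* Every one of the 180 participants is above 15% by inclusion, so the observed proportion among them is 100% by design. Only the audit report on the practice populations can supply a prevalence. That report passes through several filters: practice selection, volunteering, the nurse, payment and software conditions, attendance within two years, and recorded data sufficient for a score. None of these has a known selection probability for an ACT resident.
2. *Characteristics of high-risk people.* The 180 participants could supply these. But the sample-size section expects losses from poor recall response and from failure to join or complete of up to 80% of eligible patients in some practices. This adds patient self-selection to practice self-selection.

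Under either reading the sample is not a probability sample of the ACT.

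**Size of the clustering effect, if practice were ignored.** Inputs from the article: k = 6 practices, and m = 30 for participants. Assumed, because the article does not give them: scored patients per practice m, ICC, prevalence p = 0.10, and a 95% level for proportions.

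- Design effect: DE = 1 + (m - 1) x ICC.
- Interval ignoring practice, half-width: 1.96 x sqrt(p(1 - p)/(6m)).
- Interval allowing for six practices, half-width: 2.571 x sqrt(DE) x sqrt(p(1 - p)/(6m)), where 2.571 is the 97.5% point of t on 5 df.
- Ratio of the two: sqrt(DE) x 2.571/1.960 = sqrt(DE) x 1.31. It does not depend on p.

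At m = 1,000, the interval ignoring practice has half-width 1.96 x sqrt(0.09/6,000) = 0.76 points.

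- ICC 0.002: DE = 1 + 999 x 0.002 = 3.00; ratio 1.73 x 1.31 = 2.3; half-width about 1.7 points.
- ICC 0.01: DE = 1 + 999 x 0.01 = 10.99; ratio 3.32 x 1.31 = 4.3; half-width 3.3 points.

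Sensitivity to the assumed inputs:

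| Patients per practice | ICC | Ratio of widths |
|---|---|---|
| 30 (participants only) | 0.005 to 0.05 | 1.40 to 2.05 |
| 200 | 0.005 to 0.05 | 1.85 to 4.34 |
| 1,000 | 0.002 to 0.01 | 2.3 to 4.3 |
| 1,000 | 0.005 to 0.05 | 3.21 to 9.36 |
| 3,000 | 0.002 to 0.01 | 3.5 to 7.3 |

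At m = 3,000 and p = 0.10 the half-widths are 0.44 points ignoring practice and 1.5 to 3.2 points allowing for it. That case would imply 3,000 x 0.10 = 300 high-risk patients per practice, of whom 60 remain after an 80% loss. This is twice the target of 30 and sits awkwardly with a plan to recall as many eligible patients as possible, so 1,000 is the more cautious illustration.

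None of these ratios includes selection error, which the data cannot measure and which clustering methods do not remove.

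**The case against.** Four points can be made for the plan.

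*The practices were chosen to reflect the region.* The article does say that they were selected to represent its socioeconomic and demographic make-up broadly. This is an argument for a projection with stated assumptions. It does not create a sampling design, and it says nothing about volunteering, software, recent attendance or completeness of records.

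*The limitations are already disclosed.* The limitations section does list voluntary entry, small scale and the single city. It does not connect them to this estimate, whose target remains the whole ACT. The two sections need to be reconciled.

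*No faulty interval is specified.* This stands. A reader might infer from the other tests named in the section, none of which allows for practice, that an ordinary binomial interval is intended. The article does not say so, and the method may be set out in an analysis plan that is not shown. The clustering arithmetic is therefore conditional and is not a charge against a stated method.

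*The estimate is minor.* This also stands. It is not the primary outcome and is not named among the study's three aims.

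**Conclusion.** The concern holds in a limited form. The stated target, an ACT population proportion with a confidence interval, is one that this design cannot support without qualification, whichever way the sentence is read and whatever interval formula is used. That conclusion rests only on what the article says and needs no assumed figure.

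The clustering point is secondary. An interval that ignored practice would be about 2.3 to 4.3 times too narrow at 1,000 scored patients per practice and ICC 0.002 to 0.01, both assumed.

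Three stronger readings are tempting but unsupported:

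- **That the interval will be several times too narrow.** Practice size and ICC are not in the article, no unclustered interval is specified, and at 30 patients per practice the ratio is only 1.40 to 2.05.
- **That the proportion is biased upward because higher-risk people are more likely to have risk factors recorded.** The article gives no evidence on direction, and its planned work on recording would itself change who is scored.
- **That nothing can be estimated.** A proportion for scored recent attenders of these six practices can be reported.

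This is a worthwhile correction to a descriptive output. It does not bear on the primary analysis of CVAR change.

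**What to change.** Replace the sentence with text to this effect: *The proportion with CVAR >15% will be reported for patients with a calculable CVAR who attended one of the six pilot practices in the last two years, by practice (with the range across practices) and pooled, together with the proportion of attenders whose CVAR cannot be calculated.*

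Delete the ACT population claim. If an ACT projection is wanted, label it as age-sex standardised, state the assumption that the six practices stand for ACT practices, and give an interval based on between-practice variation (5 df). That interval belongs only to the projection. When the target is the six practices' own patients, the practices are not a sample of anything wider, and variation between them is not sampling error.

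The cost is one or two sentences, a narrower claim, and a wider interval for any projection. The audit report is already planned. The one additional figure is the count of recent attenders without a score.

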#### Qualitative Data Analysis

The thematic analysis of focus groups, semistructured interviews, reflective diaries, and key policy and program documents will be undertaken. A mixed deductive and inductive approach will be used for the analysis, which allows for initial codes to be identified from the literature, and knowledge and experience of the research team [44]. These codes will then be revised, reviewed, replaced, and added to, from the data. This process provides the inductive aspects of the analysis. Consistent with a convergent parallel mixed methods design and case study approach, the data analysis stage will include the integration of the data once the primary analysis is complete [45]. This approach will allow for the triangulation of the data to enhance validity, will help to describe the complex multi-strategy nature of *HeartLink,* and could enlighten areas of interest and relevance where empirical outcomes are not clear. This integrated analysis will be presented as the case study narrative, informing the development of the implementation model.

## Results

The *HeartLink* intervention is complete, with post intervention data collection currently underway. The results are expected in late 2015.

## Discussion

### The Model for Prevention Study

This protocol seeks to provide a detailed description of the MoFoP study, which will examine a whole-of-system CVD prevention intervention in primary health care. It will aim to identify key elements of an effective model and implementation strategies to inform better practice in this key health priority area for Australia. A recent systematic review of interventions aimed at enhancing best practice in primary health care for chronic disease management, prevention, and episodic care found that multiple and linked strategies targeting the system, practice, and community level are most likely to improve access for patients to best practice [46]. The *HeartLink* intervention, which is the focus of the MoFoP study, adopts an intersectoral and multi-level approach, which aligns with findings of this review.

Gaining a better understanding of CVD prevention in primary health care requires a research approach that can capture and express its complexity. By choosing a mixed methods research design and using the complementary case study and experimental approaches, we aim to provide a comprehensive picture of the study outcomes. While there are a number of challenges in effectively capturing the many layers in a “real life” intervention, the potential for findings to have more rapid translation into policy and practice because they present a more complete and pragmatic understanding of issues makes the approach worth pursuing.

By bringing together a range of issues of interest to contemporary primary health care, the MoFoP study provides a timely appraisal of the use of a CVAR approach to CVD prevention, the evolving role of the primary health care sector, and evidence-based approaches to supporting lifestyle change. These issues align with the current health reform agenda in Australia that commits to a reorientation of health services for a stronger preventative focus and rededication to the ideals of primary health care [38].

Finally, the MoFoP study uses existing models for improvements in chronic disease prevention as its working framework. The ECCM in particular provides a vision for an integrated, whole-of-system and intersectoral approach to CVD prevention. By developing an intervention that addresses the key elements of this model, and then undertaking a comprehensive exploration of the intervention outcomes, we hope to explore the potential to further develop the ECCM model, improving its applicability to CVD prevention in the Australian primary health care context. We also hope that an enhanced model based on the study findings will be a valuable additional outcome from the study, and will facilitate the communication and implementation of knowledge gained from this study.

### Limitations of the Study Protocol

There are a number of limitations of this study. Case study approaches have often been criticized for their lack of generalizability, and their lack of rigor. To address this, a sound research design has been developed that follows a logical process [22]. The multiple sources of data and the addition of the preexperimental component should add rigor by allowing the cross-validation of the interpretation of the study findings.

The *HeartLink* intervention itself has limitations that include the small scale of the intervention, “opt in” in the sample of practices, and the intervention occurring in one relatively small city of approximately 340,000 people. Given its pragmatic design, the study has limitations in standardizing some aspects of the intervention protocols and data collection, within busy general practices with a varied workforce and a wide range of skill sets. That acknowledged, the MoFoP study and the *HeartLink* intervention are designed to inform a larger cluster randomized controlled trial to evaluate the effectiveness of using a larger number of control and intervention practices, and to better understand the effectiveness and generalizability across the primary health care sector as a whole.

### Conclusions

The MoFoP study will examine a whole-of-system CVD prevention intervention that supports patients from risk identification through to clinical and lifestyle issues management, from general practice and into the community. By considering existing chronic disease prevention models and undertaking a holistic investigation of the *HeartLink “*case”, the MoFoP study aims to build understanding and propose new directions for this complex area of primary health care. Given the size of the problem and the current evidence to practice gap, it is an area worthy of exploration, and its outcomes should be of interest to both practitioners and policy makers.

## Abbreviations

ACT: Australian Capital Territory
CCM: Chronic Care Model
CVAR: cardiovascular absolute risk
CVD: cardiovascular disease
ECCM: Expanded Chronic Care Model
GP: general practitioner
HCA: Health Change Australia
MoFoP: model for prevention
SF: short form
